**Figure 3 figure3:**
[figure not shown]
Good School Toolkit exposure by calendar year and across school grade. Boldface school grade denotes school grade at Wave 1 survey. Grey shade indicates students’ expected Toolkit intervention exposure, showing grades and duration of exposure. *At Wave 1 all cohort adolescents were students in primary school grades P5-P7 (approx. aged 11-14) and at Wave 2 cohort adolescents are expected to be either in secondary school grades (S2-S5) or no longer attending a school (approx. aged 16-19).

### Ethics and Consent to Participate

The Contexts of Violence in Adolescence Cohort (CoVAC) study, which encompasses this long-term follow-up, was approved by the London School of Hygiene and Tropical Medicine (6183 and 14768), University of London, Institute of Education, Research Ethics Committee (1091), Uganda Virus Research Institute and Uganda National Council of Science and Technology ethics committees (SS2520 and SS4722). All adult participants and emancipated minors complete voluntary informed written consent procedures prior to involvement in the study. For adolescents under 18 years old who are not emancipated minors, caregivers are provided with information about the study and can verbally opt their children out of participation and, if the caregiver has not opted-out the adolescent, the adolescent provides voluntary informed written assent prior to involvement in the study. Consent procedures have been approved by all ethics committees. During Wave 2, survey referral was offered to adolescents based on predefined criteria agreed with service providers that related to the severity and timing of violence and/or mental health concerns reported. All were offered counseling regardless of what they disclosed. Wave 1 [26] and Wave 2 [46] protocols, including methods and referral procedures [47], are fully documented elsewhere.

### Good School Toolkit Exposure Measures

#### Primary

Participants in 21 trial intervention schools and those in the 21 wait-list control schools are categorized as the original study arms (1) trial and (2) wait-list control. Further subcategories defined within the wait-list control are adolescents who were attending Primary 5 or 6 in the 19 later delivery schools as the (2.1) later delivery exposure group; adolescents who attended one of the schools that did not implement the toolkit or who were attending Primary 7 in one of 19 later delivery schools at Wave 1 (as these students are expected to have left school prior to intervention delivery) as the (2.2) no exposure group (Figure 3).

#### Secondary

Adolescent Good School Toolkit exposure will be further defined using the following data: number of years exposed; time elapsed since exposure; age at exposure; individual survey responses to 2 exposure survey questions on role and participation in the Good School Toolkit intervention; and Raising Voices’ staff assessments of school implementation. Raising Voices’ assessments were captured during in-school visit observations by program staff across 39 schools in 2017 using a standardized scorecard developed by Raising Voices (data were not captured in one trial intervention school that reported they had discontinued the intervention and the 2 wait-list control schools that did not implement the intervention). We will use methods such as exploratory factor analysis to create composite exposure groupings; methods and construction of exposure measures will be fully documented [48,49]. For example, school implementation intensity, length of time exposed, and time since exposure may be used to generate high-, medium- and low-exposure groupings.

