**Retention in school outcomes**				
		Staying in school	Last school grade completed will be assessed in relation to current age and grade at Wave 1, for example, binary outcomes: completion of grade Primary 7 (yes=1, no=0), transition to secondary school measured as completion of grade Secondary 1 (yes=1, no=0)	Not applicable

The primary outcome is peer violence victimization. A peer is defined as students, coworkers, or community members of a similar age. Adolescents’ self-reported experience of peer violence in the last year will be measured using an adapted subset of questions from the International Society for the Prevention of Child Abuse and Neglect Child Abuse Screening Tool—Child: Institutional [61]. Questions were previously piloted and used in the Wave 1 survey [32]. For this analysis, peer violence is defined as violence from students, coworkers, or community members of a similar age. Experience of past-year peer violence will be constructed as a composite binary measure, with positive responses to one or more question items on acts of physical, emotional, and sexual violence coded as 1, and no acts coded as 0.

Secondary violence outcomes will be constructed as single and composite binary measures—as described above—for the primary outcome. Secondary violence outcome measures include past-year self-reported use of peer violence, girls’ experience and boys’ use of intimate-partner violence, measured using question items from the WHO multicountry Study on Women’s Health and Domestic Violence [51] and Conflict in Adolescent Dating Relationships Inventory [52,53,62] adapted and used during Wave 1. Intimate partners include boy/girlfriends, husbands/wives, and casual dating partners. Self-reported intimate-partner violence will be explored as a combined measure and separately by violence type (emotional, physical, and sexual).

We will measure attitudes toward teacher violence with a 3-item measure developed for the Good Schools Study and used during the Wave 1 survey [41]. A shortened 18-item Gender Equitable Men scale, previously validated among Ugandan adolescents [54], will be used to measure gender-equitable attitudes. Question items and subsets of questions, including attitudes toward domestic violence, will be explored as single items and composite outcomes. Response options for all attitude questions are on a 4-point Likert-type scale.

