### Potential Confounders and Effect Modifiers

The following factors have been identified a priori as potential confounders or effect-modifiers to the exposure-outcome relationships of interest: biological sex and the number of meals eaten the previous day (as a proxy for socioeconomic status that is expected to be associated with staying in the study school throughout intervention delivery and associated with later violence outcomes). In addition, and as appropriate for specific exposure-outcome relationships, the following variables have been identified as potential effect-modifiers or confounders measured at Wave 1: school grade, family connectedness, and experiences of violence outside of school [68,69].

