### Regression Analysis Strategy

All analysis is exploratory and hypotheses generating rather than testing. To explore if the intervention influences later outcomes, we will compare across the trial and no exposure groups (1 vs 2.2) and original study arms (1 vs 2) first including all 42 schools and then repeated, dropping the 2 nonimplementation schools. To further explore differences between levels of exposure, we plan to compare between trial and the later delivery groups (1 vs 2.1) and across secondary exposure groupings (Figure 3). We will account for clustering by including original study primary school as a random effect in mixed-effect regression models [71]. Binary outcomes will be analyzed using mixed-effect logistic regression, with effect size presented as odds ratios. Continuous outcomes will be analyzed using mixed-effects linear regression, with effect size presented as mean difference. All unadjusted and adjusted analyses will include baseline school-level mean of outcomes, where available [72]. Adjusted models will additionally include covariates identified as potential confounders. All measures of effect will be presented with 95% confidence intervals and *P* values. Size and direction of effect will be considered along with *P* values when assessing the strength of associations [70]. Appropriate methods will be used to analyze numeric outcomes that are not normally distributed. For example, bias-corrected 95% confidence intervals will be estimated using nonparametric bootstrapping. The presence of effect modification will be assessed by comparing models fitted with and without an interaction term. Likelihood ratio tests with *P* values<.1, along with the direction and size of effect for each group, will be considered as evidence for or against modification. If there is evidence of modification, then stratum-specific effects will be calculated [73].

For self-reported exposure, propensity score–matching will be used to account for the likelihood that self-reported exposure is confounded by an individual’s propensity to report exposure. We will estimate what factors predict toolkit exposure using regression analysis [29], then calculate predicted probability of exposure and group adolescents with similar propensity scores. The analysis will compare outcomes across these propensity score exposure groups, including the score as a covariate in regression models [72].

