For the primary peer-violence victimization outcome, we will present unadjusted and adjusted mixed-effect logistic regression models exploring the association between intervention exposure measures and peer-violence victimization.

For the secondary outcomes, we will present unadjusted and adjusted mixed-effect logistic or linear regression models exploring the association between intervention exposure measures and secondary outcomes. The effect of intervention exposure on secondary outcome measures will be assessed by the size of effects and accompanying *P* value and 95% confidence intervals, as well as expected direction and consistency across results.

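### Self-reported participation, and years exposed if counted from attendance, depend partly on staying in primary school and should not serve as exposures for the retention outcomes

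*Protocol article*

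**What the plan says.** The Secondary part of Good School Toolkit Exposure Measures lists, among other data, "number of years exposed; time elapsed since exposure; age at exposure; individual survey responses to 2 exposure survey questions on role and participation". It adds that "school implementation intensity, length of time exposed, and time since exposure may be used to generate high-, medium- and low-exposure groupings".

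Table 2 makes retention a secondary outcome: "Last school grade completed will be assessed in relation to current age and grade at Wave 1", with the binary examples "completion of grade Primary 7 (yes=1, no=0), transition to secondary school measured as completion of grade Secondary 1 (yes=1, no=0".

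The Regression Analysis Strategy then plans models "exploring the association between intervention exposure measures and secondary outcomes". No outcome is exempted. It says that secondary results will be judged on effect size, P value and confidence interval, and also on whether the direction is as expected and the results are consistent.

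Two other places bear on the point. Potential Confounders and Effect Modifiers justifies the number of meals as a socioeconomic proxy "expected to be associated with staying in the study school throughout intervention delivery". The caption of Figure 3 describes "expected Toolkit intervention exposure, showing grades and duration of exposure", and the Regression Analysis Strategy cites that figure: "we plan to compare between trial and the later delivery groups (1 vs 2.1) and across secondary exposure groupings (Figure 3").

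**The concern.** An exposure that a pupil can acquire only by remaining in the study primary school should not be used to explain whether pupils remain in school. Delivery in the 19 later-delivery schools began in 2015. A pupil in Primary 5 or 6 there in 2014 who left education before then could not take part, and is also unlikely to have completed Primary 7 or Secondary 1. The exposed group is therefore partly selected on the outcome.

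The planned adjustments do not reach this. The propensity score is aimed at a pupil's tendency to report exposure. The listed covariates are background factors, several of them fixed at Wave 1. They can predict who will leave, but they do not undo the fact that leaving ends the opportunity to be exposed.

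Retention is the fourth research question, and the conceptual framework expects exposed pupils to stay in school longer. The artefact runs in that direction, so under the plan's own reading rule it would count as support.

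**Working it through.** No figure in the protocol bears on this point, so there is none to reproduce. The check has two steps, both with the toolkit effect on retention set to zero.

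**Step 1: hand calculation for a Primary 6 pupil of 2014 in a later-delivery school.** Assume yearly dropout q at each year end, a chance r = 0.3 of reporting participation after one exposed year, and no grade repetition or transfer. The pupil is exposed only by attending in 2015 and completes Secondary 1 only by also not dropping out at the end of 2015.

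- Participants all attended in 2015. Their Secondary 1 completion is 1 − q, with odds (1 − q)/q.
- Non-participants make up 1 − (1 − q)r of pupils. Of all pupils, (1 − q)²(1 − r) are non-participants who complete Secondary 1.

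For q = 0.10:

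- Participants: completion 0.90, odds 9.
- Non-participants: 1 − 0.9 × 0.3 = 0.73. Completers: 0.81 × 0.7 = 0.567. Completion: 0.567/0.73 = 0.777. Odds: 0.567/0.163 = 3.48.
- Odds ratio: 9/3.48 = 2.6.

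For q = 0.05: 19/(0.63175/0.08325) = 19/7.59 = 2.5. For q = 0.20: 4/(0.448/0.312) = 4/1.436 = 2.8.

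Transfer does not reverse the sign if pupils who move to another school later drop out at the same rate as those who stay. Completion among non-participants is then (1 − q) times the share of them still in any school. That is below 1 − q whenever anyone leaves education at the end of 2014.

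**Step 2: null simulation of the cohort.**

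Inputs from the protocol: 2402 pupils (Power to Detect a Difference: 0.70 × 3431 = 2401.7); 42 schools, of which 21 trial, 19 later delivery and 2 not implementing; Wave 1 grades Primary 5 to 7.

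Assumptions not in the protocol: equal numbers per grade; yearly dropout of 5%, 10% or 20%; grade repetition of 0% or 10%; reporting probability 1 − 0.7^years; between-school SD 0.4 and between-pupil SD 0.7 on the logit scale; two years credited to trial pupils before 2014; no transfer. That credit is more than the 18 months of delivery stated for the 2014 endline. It affects the whole-sample figures but not those within later-delivery schools.

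Each setting had 200 runs. The model was logistic regression of Secondary 1 completion on exposure and Wave 1 grade, with cluster-robust errors by school in place of the planned random effect.

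| Exposure | Pupils | Median OR across settings | Runs with P<0.05 |
|---|---|---|---|
| Self-reported participation | all | 1.48-1.64 | 77-97% |
| Self-reported participation | later delivery, Primary 5-6 | 2.14-3.50 | 94-100% |
| Realised years, per year | all | 1.17-1.29 | 92-100% |
| Realised years, 10% repetition | later delivery, Primary 5-6 | 3.81-8.06 | 100% |
| Realised years, 10% repetition | trial, Primary 5-6 | 3.91-8.13 | 99-100% |
| Expected years, per year | all | 1.01 | 6-9% |
| Trial arm versus the rest | all | 1.01-1.05 | 5-9% |

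In the rows for self-report and realised years, every significant result was positive. Without repetition, realised years within Primary 5-6 gave near-complete separation and no usable odds ratio. With 200 runs, the simulation error around a 5% rejection rate is √(0.05 × 0.95/200) = 1.5 percentage points.

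**The case against.** The strongest objection concerns years exposed. A reader might infer that this measure is circular by construction and must produce a false dose-response. The protocol does not support that. It nowhere says that years are counted from attendance. Figure 3 shows expected exposure, and the analysis section cites that figure for the secondary groupings. Expected years depend only on school and Wave 1 grade, and with grade in the model they gave an odds ratio of 1.01. This stands: for years exposed the concern is conditional on a definition that the text leaves open.

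A reader might also infer that a later-delivery pupil with no exposed years has failed Primary 7 by definition. That is too strong. The outcome is last grade completed, with no requirement that it be in a study school, so a pupil who transferred can complete Primary 7 with no exposure. Repeaters gain years without gaining grades. Both weaken the dependence without removing it, provided that transferring pupils do not have markedly better retention.

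Third, the question whether the intervention influences later outcomes is assigned to trial versus no exposure and to the original arms. Secondary groupings only explore levels of exposure further, and all analysis is declared exploratory. This limits the consequence. But a hypothesis produced by the way exposure is acquired is still misleading, and the plan would weigh it for direction and consistency.

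Fourth, every Wave 1 pupil was in school in 2014, so trial-arm exposure up to then cannot depend on later dropout. That is correct. It is why the problem is greatest in the later-delivery schools.

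Lastly, the covariates go beyond meals: sex, Wave 1 grade, family connectedness and violence outside school are also listed. None of them records whether the pupil was still attending from 2015. The protocol promises to document how exposure measures are built, which could settle the definition of years but not the problem with self-report.

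**Conclusion.** The point holds for self-reported role and participation on any reading of the text, and for years exposed only if they are realised years. Related to completion of Primary 7 or Secondary 1, these measures would tend to show a positive association with no toolkit effect, above all among Primary 5-6 pupils of the later-delivery schools.

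Under the assumptions above, the null odds ratio for Secondary 1 completion is about 1.5-1.6 for self-report overall, 2.1-3.5 in later-delivery Primary 5-6 pupils, and 1.2-1.3 per realised year. These sizes depend on assumed dropout, repetition and reporting rates, and the wording of the two survey questions is not given. The direction was the same in every setting tried.

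The mechanism does not touch the primary exposure groups, the school scorecard, trial-arm exposure up to 2014, or expected years once Wave 1 grade is adjusted for. A reader who concludes that the fourth research question cannot be answered goes further than the documents allow: the arm and primary-group comparisons remain available for it.

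**What to change.** For the retention outcomes, use only exposure fixed at Wave 1: the original arm, the primary exposure groups, or expected years from school and Wave 1 grade as in Figure 3. Include Wave 1 grade in those models as a rule; at present it is listed only for use where appropriate. Exclude self-reported participation, any duration counted from attendance, and any composite grouping that contains either.

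In the Secondary exposure section, state that number of years exposed means expected years, not years attended.

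The cost is a sentence or two and a few fewer exploratory models. What is lost is an individual-level dose analysis for retention. The protocol reports that data analysis has not been conducted, so the change can be made before results are seen.

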### Study Outcome Measures

Study outcome measures are summarized in Table 2.

**Table 2 table2:** Summary of the study outcome measures.

Outcomes			Measure construct	Source
**Violence outcomes:**				
	**Primary outcome:**			
		Peer violence victimization: Self-reported experience of any physical, emotional, and sexual violence between adolescent peers, in the last 12 months.	Question items on physical (6 items), emotional (4 items), and sexual violence (4 items) experienced from a peer, constructed as a binary outcome. Positive response to 1 or more of the 16 items coded=1, negative to all items coded=0. Binary outcomes will also be constructed separately by violence type (physical, emotional, and sexual). A peer is defined as students, coworkers, or community members of a similar age.	Questions adapted from the International Society for the Prevention of Child Abuse and Neglect Child Abuse Screening Tool-Child Institutional [50].
	**Secondary outcomes:**			
		Peer violence perpetration: Self-reported use of physical and emotional violence between adolescent peers, in the last 12 months.	Questions items on physical (2 items) and emotional violence (3 items) use against a peer, constructed as a binary outcome. Positive response to 1 or more of the 5 items coded=1, negative to all items coded=0. Binary outcomes also constructed separately by violence type (physical and emotional). A peer is defined as students, coworkers, or community members of a similar age.	Questions adapted from the International Society for the Prevention of Child Abuse and Neglect Child Abuse Screening Tool-Child Institutional [50]
		Intimate-partner violence victimization: Self-reported experience of physical, emotional, and sexual intimate-partner violence among ever partnered adolescent women, in the last 12 months.	Question items on physical (3 items), emotional (8 items), and sexual violence (4 items) experienced from a partner, constructed as a binary outcome. Positive response to one or more of the 15 items coded=1, negative to all items coded=0. Binary outcomes also constructed separately by violence type (physical, emotional, and sexual). Intimate partners include boy/girlfriends, husbands/wives, and casual dating partners.	Adapted from the World Health Organization multicountry study on women’s health and domestic violence against women [51], and the Conflict in Adolescent Dating Relationships Inventory [52,53]
		Intimate-partner violence perpetration: Self-reported use of physical and emotional intimate-partner violence, among ever partnered adolescent men, in the last 12 months.	Question items on physical (2 items) and emotional (3 items) violence use constructed as a binary outcome. Positive response to one or more of the 5 items coded=1, negative to all items coded=0. Binary outcomes also constructed separately by violence type (physical and emotional). Intimate partners include boy/girlfriends, husbands/wives, and casual dating partners.	Adapted from the World Health Organization multicountry study on women’s health and domestic violence against women [51], and the Conflict in Adolescent Dating Relationships Inventory [52,53]

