**Methods:**

This is a nonrandomized quasi-experimental 4-year follow-up study of adolescents who attended the 42 Good Schools Study primary schools in 2014; 21 schools initiated the Good School Toolkit intervention during the trial from 2012, and 19 schools initiated the intervention after the trial (during the later delivery phase) from 2015; 2 schools did not implement the intervention. Students in the final school grade (Primary 7) during 2014 of the 19 primary schools in the later delivery phase are expected to have left school prior to toolkit delivery in 2015. Wave 1 data were collected in 2014 from 3431 grade Primary 5 to Primary 7 school students aged 11-14 years; these students were followed up in 2018-2019 when aged 16-19 years and invited to participate in the Wave 2 survey. Data were collected in face-to-face interviews by trained Ugandan field researchers. Toolkit exposure groups are defined as exposed during the Good Schools Study trial (from 2012), as exposed during later delivery (from 2015), or not exposed including those expected to have completed Primary 7 prior to later delivery or from the 2 schools that did not implement the toolkit. Associations between outcomes at Wave 2 and toolkit exposure groups will be analyzed using mixed-effect multivariable logistic and linear regression models for binary and continuous outcomes, respectively. This analysis is exploratory and aims to generate hypotheses on if, and under what circumstances, the toolkit influences later adolescent outcomes.

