### Long-Term Effects: Conceptual Framework

A schematic that illustrates mechanisms through which the Good School Toolkit may achieve long-term effects is shown in Figure 2. The Good Schools Study’s quantitative and qualitative findings suggested that the toolkit intervention improved the schools’ operational culture and enhanced student capabilities, including improvements in student-teacher relationships; fostered attitudes that were less accepting of teacher violence; enhanced emotional support from peers; allowed enhanced school-connectedness; and improved self-regulation, voice, and motivation [28,31,39-41]. We hypothesize that students who experienced the toolkit intervention during their primary education (ie, were exposed to a supportive culture and less violence in a safer school environment) are less likely to drop out of school and therefore are retained in the education system for longer. Furthermore, we hypothesize that students’ enhanced capabilities—brought about by the toolkit intervention—can be retained through the transition out of primary school into new environments, equipping adolescents with individual skills supportive of resilience. Through these positive changes brought about by exposure to the toolkit intervention, we hypothesize that adolescents will have attitudes that are less accepting of violence, will be more gender-equitable, and will be less likely to perpetrate or experience peer and intimate partner violence in later adolescent relationships.

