### Research Questions

We aim to evaluate long-term effects of the Good School Toolkit, specifically whether exposure to the toolkit intervention in early adolescence is associated with (1) less violent relationships in later adolescence, including peer-violence victimization (primary outcome), peer-violence perpetration, and intimate-partner violence victimization among female adolescents and perpetration among male adolescents; (2) lower acceptance of teacher violence and more equitable gender attitudes in later adolescence; (3) factors supportive of resilience in later adolescence (enhanced agency, self-regulation, peer connectedness, and social and psychological assets); and (4) increased retention in school.

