### Sampling, Intervention Delivery, and Survey Assessments

The original Good Schools Study trial sampling is fully described elsewhere [26]. In summary, we used the 2010 list of 268 government and nongovernment primary schools in Luwero district, obtained from the Ministry of Education. Eligibility criteria were school size (>40 Primary 5 students) and having no existing interventions. Of 151 eligible primary schools that were identified and stratified into 3 groups based on the student male to female ratio (>60% girls, >60% boys, or approximately even), 42 schools were randomly selected proportional to the size of stratum. All selected school headteachers agreed for their school to participate. After the trial baseline survey in 2012, stratified block randomization was used to allocate schools to receive the intervention immediately or to be wait-listed to receive the intervention after the end of the trial (Figure 3). Stratified randomization was used to ensure balance regarding the following key factors: baseline violence, whether the school was urban or rural, and a qualitative assessment of the likelihood of attrition throughout the trial. For both the trial baseline (in 2012) and endline (in 2014), for cross-sectional surveys, a simple random sample of up to 130 Primary 5 to Primary 7 students per school were invited to consent for a survey interview, and if there were <130 Primary 5 to 7 students then all were invited. Figure 2 describes the timing of the Good School Toolkit delivery and survey assessments. The trial baseline survey data were collected across the 42 schools in 2012 (n=3706, 77% survey response). In 2014, after 18 months of Good School Toolkit implementation in the 21 intervention schools, trial endline data were captured across the 42 schools (n=3820, 93% survey response). Of the students surveyed at the trial endline, 90% (n=3431) agreed to be followed up. These individuals constituted our Wave 1 sample for this study and analysis. The Good School Toolkit intervention was subsequently delivered to 19 of the 21 wait-list control schools from 2015, by which time the Primary 7 students were expected to have left primary school, and 2 wait-list control schools declined to implement the toolkit. Wave 1 adolescents were traced, and Wave 2 survey data collected during 2018 and 2019. A full description of data collection procedures and methods for our Wave 2 survey are reported elsewhere [46].

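### Both partner-violence outcomes are restricted to ever-partnered adolescents, a status formed largely after exposure; whole-sample and partnering results belong beside them

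*Protocol article*

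**What the plan says.** Table 2 sets the denominators. Victimization is "Self-reported experience of physical, emotional, and sexual intimate-partner violence among ever partnered adolescent women, in the last 12 months"; perpetration is "Self-reported use of physical and emotional intimate-partner violence, among ever partnered adolescent men, in the last 12 months". The definition of a partner is broad: "Intimate partners include boy/girlfriends, husbands/wives, and casual dating partners".

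The Research Questions section puts the question more widely, as "intimate-partner violence victimization among female adolescents and perpetration among male adolescents". The text after Table 2 likewise speaks of girls and boys and does not mention partnering.

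On timing, the Wave 1 survey in 2014 took place "after 18 months of Good School Toolkit implementation in the 21 intervention schools", and the abstract says "these students were followed up in 2018-2019 when aged 16-19 years". Under the conceptual framework, exposed students are expected to hold more gender-equitable attitudes and "are less likely to drop out of school and therefore are retained in the education system for longer".

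The Regression Analysis Strategy compares the trial group with the no-exposure group (1 vs 2.2) and the original arms (1 vs 2). Adjusted models add potential confounders; Wave 1 school grade is listed among those to be used as appropriate. The Limitations section discusses selection through refusal of follow-up and through attrition, but not through partnering.

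**The concern.** Students were 11-14 at Wave 1, and trial schools had begun the toolkit before then. Much of what makes someone ever partnered at 16-19 therefore probably happened after exposure started. Longer schooling and more equitable attitudes are plausible routes to fewer, later or different partnerships. Restricting the analysis to the ever-partnered then conditions on something the toolkit may have changed, and the partnered members of the two groups may no longer be comparable. In the arm comparison (1 vs 2), which rests on randomised schools, this adds a selection made after randomisation.

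At stake is the reading of two secondary outcomes. The article will judge secondary outcomes partly on whether effects point in the expected direction and agree with one another, and it says that an absence of long-term effects would suggest further efforts are needed. A direction produced by selection into partnership would feed both judgements.

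**Working it through.** The article gives no share ever partnered and no partner-violence rate, so there is no figure of its own to reproduce on this point. What follows shows what the restriction can do on assumed inputs. It does not estimate what it will do.

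**Assumed inputs (girls; the same logic applies to boys)**
- Ever partnered: 60% if unexposed, 40% if exposed. So 40% of girls partner either way, and 20% partner only if unexposed.
- Violence in girls who partner either way: 40% if unexposed, 36% if exposed. True odds ratio (OR) = (0.36/0.64)/(0.40/0.60) = 0.84.
- Violence in girls who partner only if unexposed: q, varied from 10% to 80%.

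**Formulas**
- Ever-partnered, unexposed: (0.40 × 0.40 + 0.20 × q)/0.60. Ever-partnered, exposed: 0.36.
- All girls, unexposed: 0.40 × 0.40 + 0.20 × q. All girls, exposed: 0.40 × 0.36 = 0.144.

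| q | Ever-partnered: unexposed vs exposed | OR | All girls: unexposed vs exposed | OR |
|---|---|---|---|---|
| 10% | 30.0% vs 36.0% | 1.31 | 18.0% vs 14.4% | 0.77 |
| 20% | 33.3% vs 36.0% | 1.12 | 20.0% vs 14.4% | 0.67 |
| 40% | 40.0% vs 36.0% | 0.84 | 24.0% vs 14.4% | 0.53 |
| 60% | 46.7% vs 36.0% | 0.64 | 28.0% vs 14.4% | 0.43 |
| 80% | 53.3% vs 36.0% | 0.49 | 32.0% vs 14.4% | 0.36 |

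**Reading the table**
- If the avoided partnerships would have been low-risk, the partnered-only OR moves towards or past 1. If they would have been high-risk, it overstates the benefit within relationships.
- With a smaller shift in partnering (60% to 50%), the partnered-only ORs over the same q are 1.04, 0.97, 0.84, 0.74 and 0.64. Reversal then occurs only at the lowest q.
- With no effect at all in girls who partner either way, and partnering at 60% vs 40%, the partnered-only OR runs from 1.56 (q = 10%) to 0.58 (q = 80%).
- If the toolkit changes nobody's partnering (60% in both groups), the partnered-only OR is 0.84, the true value.

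**Why grade adjustment is needed**

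The no-exposure group is put at 19% of the Wave 2 sample. Assuming schools of equal size and equal follow-up, the 2 non-implementing schools supply 2/42 = 4.8 points. The other 14.2 points are Primary 7 students of the later-delivery schools, and 14.2/19 is about 75%. Older adolescents have had longer to partner, so partnering may differ in 1 vs 2.2 without any toolkit effect.

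Suppose partnering is 60% vs 52% purely through age, with violence at 40% among the partnered in both groups. The ever-partnered OR is 1.00. The whole-sample figures are 0.60 × 0.40 = 24.0% and 0.52 × 0.40 = 20.8%, so OR = (0.208/0.792)/(0.240/0.760) = 0.83, a spurious benefit.

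**The case against.** The strongest reply is that the restriction suits the question. The research question is framed as less violent relationships, and those who have had a partner are the natural group at risk. An all-girls rate mixes partnering with violence, so putting it first would be a choice of estimand and not a correction. This stands, and it is why the ever-partnered analysis should stay. It is not a complete defence: status is ever partnered while violence is counted over 12 months. Someone with a partner only before that window stays in the denominator and, reporting no acts, is coded 0. It is therefore not a clean past-year at-risk set.

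Second, no statement in the article says that the toolkit changes partnering, and the inclusion of casual dating makes delay through schooling less obvious. This also stands: the link is an inference from the conceptual framework.

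Third, a whole-sample analysis has a weakness of its own, since an age difference in partnering alone can create an apparent benefit in 1 vs 2.2. This stands unless grade is adjusted for, and it rules out the whole-sample version as an unqualified replacement.

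Fourth, shifts of the size illustrated may be too small to detect. The reversal at q = 20% is 2.7 points, against a detectable difference of 8 points stated for the larger primary-outcome sample. That is fair, but the article reads secondary outcomes on direction and consistency as well as P values.

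Finally, a reader might infer that no whole-sample version is planned. The article names none, but it condenses a fuller plan that is not shown, and its unrestricted wording elsewhere does not exclude one.

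**Conclusion.** The point holds as a limited one about estimand and interpretation. Table 2 conditions both partner-violence outcomes on a status formed largely after exposure, the toolkit could plausibly alter that status, and the research question is worded without the restriction. If the toolkit changes who partners, the partnered-only odds ratio can be wrong in either direction for the effect within relationships.

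The range of 1.31 to 0.49 around a true 0.84 rests wholly on assumed partnering shares and risks. The article supports neither a size nor a direction. A reader might infer that the planned comparison will hide or reverse a benefit. That would need both a toolkit effect on partnering and, if partnering falls, lower risk in the partnerships avoided; the article establishes neither. Nor does it establish an exact grade gap between the groups, because the grade mix is not given.

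The outcomes concerned are secondary, the analysis is declared exploratory, and the primary outcome is untouched. The change is worth making because it is cheap and uses data already collected.

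**What to change.** 1. Keep the ever-partnered analysis for both outcomes, and label it as conditional on a post-exposure status.
2. Report beside it an all-girls analysis of victimization and an all-boys analysis of perpetration, with never-partnered coded 0.
3. Analyse ever-partnered status itself as an outcome by exposure group, separately for girls and boys. Similar shares would be reassuring but not proof, because different adolescents may make up the same share.
4. Adjust all three for Wave 1 school grade as a fixed choice, and give weight to the original-arm comparison (1 vs 2), where the grade imbalance built into 1 vs 2.2 is not present by design.
5. Align the wording of the Research Questions and the text after Table 2 with the denominators used.

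The cost is one recode and a few extra models. The drawback is that the whole-sample estimate combines partnering with violence within partnerships, so the three results have to be read together.
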